## Abstract

**Background:**

Colorectal cancer (CRC) screening, such as fecal occult blood test (FOBT), is an effective way to prevent CRC, one of the most common cancers worldwide. However, studies found that South Asian ethnic minorities tend not to utilize CRC screening, whose importance on CRC prevention shall be educated among those from ethnic minorities, especially older adults. The purpose of this study is to develop and implement a family-based, multimedia intervention to augment the knowledge of CRC prevention among older South Asian adults in Hong Kong and enhance their motivation for undergoing FOBT. The acceptability and effectiveness of the intervention will be assessed using the Reach, Effectiveness, Adoption, Implementation, Maintenance (RE-AIM) framework.

**Methods:**

A cluster randomized controlled trial will be carried out. Three hundred and twenty South Asian dyads, comprising an older adult aged between 50 and 75 and a younger family member aged between 18 and 49, will be recruited in ten districts in Hong Kong through community organizations that provide support services for South Asians in local communities. Dyads will be randomly allocated to either the intervention or wait-list control group. Intervention dyads will receive intervention, whose contents are based on the health belief model, via multiple forms of media including PowerPoint presentation, video clip and health information booklet. Control dyads will receive intervention after post-intervention data are collected. For dyads in both groups, an appointment with a family doctor will be arranged for those willing to undergo FOBT. Outcomes will be assessed at baseline and post-intervention. Data will be analysed using the Generalised Linear Models Procedure in an intention-to-treat manner.

**Discussion:**

Findings of this study will provide evidence of the benefits of utilizing multimedia and family-based approaches in intervention development to enhance the effectiveness of health promotion interventions for ethnic minorities. Further, the findings would provide reference to the potential incorporation of the intervention in the existing support services for South Asian ethnic minorities in local communities.

**Trial registration:**

This trial is registered at the ISRCTN Registry (ISRCTN72829325) on 19th July 2018.

**Electronic supplementary material:**

The online version of this article (10.1186/s12889-019-6995-7) contains supplementary material, which is available to authorized users.

## Background

Colorectal cancer (CRC) is currently one of the most prevalent cancers, with more than 1.36 million new cases reported in 2012 worldwide [1]. Notably, CRC prevalence rate has been generally increasing over the past decades, with the projection of incidence at over 2.2 million by 2030 [2]. In Hong Kong, CRC appears currently as the most common cancer in terms of incidence, with more than 5000 new cases reported in 2015 [3]. More importantly, the risk of CRC rises with age, with the majority of CRC onset at the age of 50 or above [4]. The implementation of effective preventative measures against CRC development, especially among older adults, is of utmost importance to help control the growing prevalence of CRC worldwide. CRC screening strategies, such as colonoscopy and fecal occult blood test (FOBT), are proved to be effective in CRC prevention and reduction of CRC mortality [5, 6], primarily by enabling early diagnosis, thereby increasing the chance of cure through effective cancer treatment. In the light of the benefits of CRC screening in checking against CRC development, CRC screening programs have been developed and implemented worldwide [7]. Likewise, the Hong Kong government has also launched a pilot scheme to encourage utilization of CRC screening services among individuals aged between 50 and 75, who are encouraged to visit their family doctors for an FOBT. Those with detectable amount of blood in their stool will be asked to undergo colonoscopy examination for further assessment of signs of CRC [8].

Despite the availability of CRC screening programs to the public, previous studies showed that ethnic minorities tend not to undergo CRC screening, as evidenced by the lower utilization rate of CRC screening services by ethnic minorities compared to the general population [9–15]. Indeed, a recent systematic review also revealed that being a member of the ethnic minorities is one of the barriers that discouraged the utilization of CRC screening [16]. Previously, studies had revealed a number of factors that could contribute to this phenomenon, including lack of knowledge of CRC and its preventive measures, embarrassment, lack of recommendations on physicians and limited access to healthcare [17–20]. These findings suggest that development and implementation of educational interventions dedicated to enhancing the knowledge of ethnic minorities on CRC prevention, as well as their self-efficacy and motivation to utilize CRC screening would be necessary to increase their uptake of screening. With South Asians being one of the largest and fast-growing populations in Hong Kong [21], they should be targeted in such health-related interventions to address the ethnic disparities in CRC screening utilization in Hong Kong [14].

Previously, studies were conducted in various Western countries to evaluate the effectiveness of certain interventions in reducing the existing disparity in the utilization of CRC screening services between ethnic minorities and the general population. A systematic review published by Naylor et al. had summarized their findings [22]. Overall, the review demonstrated that interventions involving the provision of education on CRC and its preventive measures to ethnic minorities via culturally- tailored materials, alongside navigation services, would enhance the uptake of CRC screening or adherence to CRC screening guidelines among these individuals. Likewise, systematic reviews on CRC screening interventions developed specifically for Latino [23] and Hispanic [24] ethnic minorities yielded similar findings, showing that the provision of education and navigation are key to a higher uptake of CRC screening. Notably, they also highlighted the importance of using culturally-tailored educational materials in enhancing the effectiveness of interventions. Indeed, the role of culturally-tailored interventions in enhancing the knowledge of CRC and CRC screening uptake among ethnic minorities was also demonstrated in a recent study with Hispanics in rural communities in the United States [25]. The inclusion of the above features should therefore be considered in the development of future interventions for improving CRC screening uptake among ethnic minorities.

Nevertheless, to further improve the efficacy of such interventions targeting older adults, strategies such as the involvement of family members in intervention should also be considered. A previous review had demonstrated the benefits of family involvement in enhancing the effectiveness of health-related interventions dedicated to improving health outcomes of older adults with diabetes [26]. More importantly, family support was shown in a qualitative study to be a major factor that may modify the CRC screening behaviours of older South Asian adults [27]. For example, older adults were more reliant on their younger family members in interpreting written materials for health information, and the participation of older adults in CRC screening programs was largely dependent on the recommendations by their descendants. The education of younger family members on the importance of screening in CRC prevention could increase the likelihood for them to recommend screening to their parents, thereby enhancing the screening uptakes of older adults. Therefore, the involvement and participation of younger family members may be conducive to interventions centring older adults.

Despite the availability of studies evaluating the effectiveness of interventions on enhancing the uptake of CRC screening among ethnic minorities, there is currently a scarcity of such studies on South Asians. As cultural relevance of intervention materials appears an important factor in the efficacy of health-related interventions for ethnic minorities, intervention materials used in previous studies on ethnic groups may not necessarily be applicable to the intervention on South Asians. There is a research gap in intervention development that addresses ethnic disparities in CRC screening uptake within communities. To address this gap, we propose to develop a family-based multimedia intervention for older South Asian adults in Hong Kong that educate them and their younger family members on CRC and the importance of screening in disease prevention. The intervention, carried out through partnership with various local South Asian community organizations, aims to enhance participants’ knowledge of CRC and increase their self-efficacy and motivation for undergoing FOBT via a local family doctor. Findings of this study will inform healthcare providers, both in Hong Kong and worldwide, of potential utility of this intervention in enhancing CRC screening uptake among older South Asian ethnic minorities for effective CRC prevention, which could potentially help reduce the global prevalence of the disease.

### Objectives

The objectives of this study are as follows:To develop and implement a family-based, culturally sensitive and linguistically appropriate multimedia intervention dedicated to enhancing the self-efficacy and motivation of older South Asian adults in Hong Kong to undergo FOBT.To evaluate whether this intervention is effective in encouraging the uptake of CRC screening and FOBT among older South Asian adults in Hong Kong through the five dimensions in the Reach, Effectiveness, Adoption, Implementation, Maintenance (RE-AIM) framework developed by Glasgow et al. in 1999 [28]. Details of the parameters in each RE-AIM dimension are outlined in the ‘Outcome Measures’ section below.To assess whether this intervention is acceptable to South Asian families in Hong Kong.

## Methods

The preparation of this study protocol follows the guidelines set out by the Standard Protocol Items: Recommendations for Interventional Trials (SPIRIT) checklist. The completed SPIRIT checklist is shown as Additional file 1. A SPIRIT figure is also provided as Fig. 1 to demonstrate the flow of the study.

**Fig. 1 Fig1:**
[figure not shown]
The SPIRIT Figure

### Design

This study will utilize a cluster randomized controlled trial design, which includes a wait-list control group.

### Study settings

Interventions will be conducted in various South Asian community centres, ethnic minority associations and non- governmental organizations that provide support services for South Asians within local communities in ten districts in Hong Kong. Partnership with these organizations will be sought prior to the implementation of the intervention, as described below. These organizations are referred as ‘partner organizations’ hereafter.

### Participants

A total of 320 dyads of older South Asian adults and their younger family members will be recruited for the study. The inclusion criteria for older adults include 1) having a South Asian origin (either Indian, Pakistani or Nepali), 2) aged between 50 and 75, 3) having a younger family member or relative aged between 18 and 49, and 4) residing in Hong Kong during subject recruitment. Those participated in our previous community-based project titled ‘A community health worker-led multimedia intervention to increase cervical cancer screening uptake among South Asian women: A randomized controlled trial’ will be excluded.

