### Sample size estimation

Sample size calculation of this study is based on the findings of a previous study on the implementation of an intervention aiming to enhance CRC screening uptake among African Americans, under which the difference in CRC screening uptake between the intervention and control groups at six-month follow up was compared [29]. The authors observed a difference of 16.2% in the proportion of intervention and control participants who had undergone screening. To reject the null hypothesis that no difference in screening uptake exists between the two groups at a 5% level of significance, both groups require 126 dyads to achieve a power of 80%. To reach an attrition rate of 20%, a total of 320 dyads shall be recruited, with 160 dyads in each group.

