#### Maintenance

The ‘Maintenance’ of the intervention will be assessed by the level of willingness for persons-in-charge of partner organizations to continue implementing our intervention at their centers after project completion. An author- developed questionnaire with a five-point rating scale will be used for the assessment.

Demographic data, including age, ethnic group, number of people in the household, monthly household income, years of formal education, marital status, employment status, number of years’ residence in Hong Kong, family history of cancer, health insurance status, acculturation and relationship of the dyad members, will also be collected by means of an author-developed questionnaire.

All questionnaires used in outcome measurement will first be developed in English and subsequently translated into Urdu, Nepali and Punjabi by our research staff member of a South Asian origin. Back-translation will be conducted to ensure content and semantic equivalence in the translated questionnaires. A panel consisting of individuals fluent in Urdu, Nepali or Punjabi, and those involved in educating South Asians on health promotion and cancer prevention will be invited to proofread the Urdu, Nepali and Punjabi versions of the questionnaire to ensure the validity of the contents.

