### Data collection procedures

Upon receipt of the informed consent, dyad participants will be asked to complete the author-developed questionnaire for the collection of demographic data (T0). At baseline and immediately after the intervention (T1), younger family members of the dyads will be asked to complete the questionnaire that assesses their willingness to encourage older family members to undergo FOBT and their readiness to assist them in collecting stool samples for the test. At T1, dyad participants will also be asked to complete the satisfaction questionnaire to indicate their level of satisfaction of the intervention. A coordinator from our research team will prepare an attendance record, recording the number of older family members of the dyads who attend medical consultation at a family doctor a month post-intervention (T2) and return the stool sample to the family doctor for FOBT 2 months after the medical consultation (T3). Data collection from the dyads in the control group will also be conducted as described above. After project completion, data collectors will approach the persons-in-charge of partner organizations for the completion of a questionnaire enquiring their level of willingness to continue implementing the intervention at their centers.

As a token of appreciation to the dyads’ participation in the intervention, our research team will offer all participants a weighing scale upon completion of baseline data collection.

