## Discussion

CRC screening is an effective way to detect precancerous lesions in colon and rectum, which enables early CRC detection. This increases the availability of treatment options and likelihood of cancer cure, thereby reducing CRC mortality [31]. Increased utilization of CRC screening would also be likely to reduce the prevalence of CRC worldwide, and should therefore be encouraged. Nevertheless, as indicated above, South Asian ethnic minorities were found to exhibit a low uptake of cancer screening, primarily due to their inadequate knowledge on cancer prevention and cultural beliefs. Moreover, our previous study also revealed that only 10% of South Asians aged 50 or above had previously undergone CRC screening [14], implying that the older generation of South Asian ethnic minorities tend not to utilize CRC screening services available to them. As CRC risks were shown to increase with age [4], the development and implementation of interventions, primarily targeting older South Asian adults, effective in promoting CRC screening uptake would be of paramount importance. Since older South Asian older were found to often rely on their younger family members in the acquisition of health-related information [27], a family-based approach would be required in the development of intervention that aims to raise the awareness on the importance of CRC screening in CRC prevention among older South Asian older adults. Here, a CRC screening intervention that targets both the younger and older members of families is proposed to enhance its effectiveness in disseminating information on CRC prevention among older South Asian older and encouraging the utilization of CRC screening. To the best of our knowledge, this is the first study dedicated to assessing the effectiveness of a family-based intervention to increase CRC screening uptake among South Asian ethnic minorities within a Chinese community.

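### The older adult's own CRC screening history is in neither the listed eligibility criteria nor the listed baseline items, so an imbalance between ten districts could be neither seen nor adjusted

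*Protocol article*

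**What the plan says.** **Eligibility (Protocol article, Participants).** The older adult must be Indian, Pakistani or Nepali, be aged 50 to 75, and meet two further criteria: "3) having a younger family member or relative aged between 18 and 49, and 4) residing in Hong Kong during subject recruitment". The one exclusion opens "Those participated in our previous community-based project titled" and names a cervical screening trial. Nothing concerns earlier CRC screening or a history of CRC.

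**Baseline data (Outcome measures, end of Maintenance).** Twelve items are listed, ending with "family history of cancer, health insurance status, acculturation and relationship of the dyad members, will also be collected". The older adult's own screening history is not among them. Data collection procedures adds only the younger member's willingness and readiness questionnaire at baseline.

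**Prior screening in the target population (Discussion).** The investigators' previous study found that "only 10% of South Asians aged 50 or above had previously undergone CRC screening".

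**Sample size (Sample size estimation).** "The authors observed a difference of 16.2% in the proportion of intervention and control participants who had undergone screening". From this, "at a 5% level of significance, both groups require 126 dyads to achieve a power of 80" percent. The control rate is not given.

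**Design and analysis.** Randomization allocates ten districts, five to each group, and mentions no matching or stratification. Under Data collection procedures, the doctor's visit is recorded one month after the intervention (T2) and the stool sample two months after the consultation (T3). Under Data analysis, uptake at T2 and T3 is compared by an unadjusted chi-squared test. Adjustment for confounders is planned only for the younger members' two repeated outcomes.

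**The concern.** The trial asks whether a talk, a video and a booklet move older adults to complete an FOBT within about three months. Someone tested recently may not be due for another test. Someone who screens regularly may return one regardless. In either case the talk has little to change, so such dyads contribute much the same result to both arms and shrink the observed difference.

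The more serious risk is imbalance. With five districts per arm, the share of previously screened older adults can differ between arms by chance, and recruitment through local organisations may add to that. Previous screening is plausibly related to later uptake. If it is not recorded at T0, nobody can check whether the arms were alike on it, and no analysis can correct for it. The only recovery is recall after the intervention, which the intervention itself may colour.

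**Working it through.** **1. Inputs.** Difference 16.2 points, 5% two-sided, 80% power, 126 per group, 160 per group enrolled (Sample size estimation; Data analysis). Ten districts, so 320/10 = 32 dyads per district on average. Previously screened: 10% (Discussion). Control rate: not stated, so assumed and varied. Clustering is ignored in steps 2 to 4.

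**2. Can 126 be reproduced?** Only by supplying a control rate. The formula used is

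n = [1.96·√(2p̄(1−p̄)) + 0.84·√(pC(1−pC) + pT(1−pT))]² / (pT − pC)²,

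where p̄ is the mean of pC and pT. With pC = 22.5% and pT = 38.7%, n = 126. With pC = 17.7% and a continuity correction, n = 126 as well. So 126 fits low control rates near 18% or 22.5%, but rates near 60–65% also come close. It cannot be pinned down. Attrition: 126/0.8 = 157.5, so 158 per group, close to the stated 160.

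**3. Dilution, as an illustration.** Let a share s of dyads have the same uptake u in both arms, and let the rest respond as planned. Then each arm's rate is (1−s)p + s·u, and the difference becomes (1−s) × 16.2. With s = 10%: 0.9 × 16.2 = 14.6 points. With s = 5% it is 15.4, and with s = 20% it is 13.0.

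Results for s = 10% and u = 0:

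| Assumed control rate | Rates after dilution | n per group, before → after | Power at 126, before → after |
|---|---|---|---|
| 18% | 16.2% v 30.8% | 115 → 132 | 84% → 78% |
| 22.5% | 20.3% v 34.8% | 126 → 147 | 80% → 74% |
| 24% | 21.6% v 36.2% | 130 → 151 | 79% → 73% |

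The power loss is about 5 to 6 points. The opposite bound, u = 100% (regular screeners who all return a sample), is harsher because it also moves both rates towards 50%. At 22.5% the rates become 30.3% v 44.8%, n is 172 and power at 126 is 67%.

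**4. The same with everyone enrolled.** If all 160 per group are analysed, diluted power at u = 0 is 87% (control 18%) or 82% (control 24%). At u = 100% it is 79% or 77%.

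**5. Imbalance.** The SD of the chance difference between arms in the share previously screened is

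√[2 × 0.10 × 0.90/160 × (1 + 31·ICC)].

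This gives 3.4 points at ICC 0, 4.3 at ICC 0.02 and 5.4 at ICC 0.05 (ICCs assumed). A split of 5% v 15% is thus about 3 SD at ICC 0 but under 2 SD at ICC 0.05. With no intervention effect and an 18% control rate, such a split alone would shift the uptake difference by 0.10 × 18 = 1.8 points if u = 0, or by 0.10 × (100 − 18) = 8.2 points if u = 100%. The direction depends on which arm has more previously screened members.

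**The case against.** **The article is condensed.** Both lists are introduced with open wording (include, including), and the T0 questionnaire is not shown. A reader might infer that screening history is certainly not collected, but the text shows only that it is not listed. This stands as a limit on certainty. The point survives because the baseline list is detailed, reaching family history of cancer and acculturation, yet omits the factor closest to the outcome.

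**The effect is not known to shrink.** A reader might infer that the trial's true target is 14.6 points, or that it is underpowered for this reason. The documents do not support that. The source study may itself have enrolled screened people, in which case 16.2 is already diluted. The 10% is people ever screened, no rescreening interval is given, and zero uptake in all of them is an assumption. Nor is 10% shown to be a ceiling among volunteers from partner organisations. And with 160 per group, unclustered power stays above 80% at the zero-uptake bound. All of this stands.

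**Balanced dilution is not bias.** Correct: it costs power only. Bias in the realised comparison needs an imbalance, which is possible but not shown.

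**Broad eligibility is legitimate.** The trial evaluates a community programme under RE-AIM, Reach included, and its age range matches the pilot scheme's. So the absence of an exclusion is not an error. A rule tied to being up to date would also need criteria that the documents do not contain.

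**A covariate would not enter a chi-squared test.** Correct, so the analysis must change along with the questionnaire.

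**Conclusion.** The concern holds as an omission in what is listed for baseline measurement, joined to an unadjusted uptake analysis. Followed as written, the plan could neither show nor correct an imbalance in previous screening across ten randomised districts. Chance differences of about 3 to 5 points (one SD, assumed ICC 0 to 0.05) in the share previously screened are ordinary at 10% prevalence. A 10-point split could shift the uptake difference by about 2 to 8 points, depending on how those members behave.

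Dilution is secondary and its size is unknown. The fall from 16.2 to 14.6 points, with a loss of 5 to 6 points of unclustered power at 126 per group, is an illustration. It rests on an assumed control rate, 10% of dyads at zero uptake in both arms, and a source study free of such people. It should not be read as a demonstrated shortfall, nor as proof that people already screened must be excluded.

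**What to change.** 1. **Participants' T0 questionnaire:** add one item on the older adult's previous CRC screening (type of test and date) and any history of CRC. If the full questionnaire already has it, say so in the protocol.
2. **Data analysis:** replace or supplement the chi-squared tests of T2 and T3 uptake with a cluster-aware model, suited to ten districts, that includes previous screening as a prespecified covariate.
3. **Data analysis:** prespecify a further analysis restricted to older adults not previously screened, and tabulate screening history by arm at baseline.
4. **Eligibility:** excluding people already up to date with screening is an option for the investigators to weigh. It would need a stated definition, and it costs a smaller pool and narrower Reach.

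Items 1 to 3 cost one extra question and a slightly more complex uptake analysis. Item 1 must be in place before baseline collection, since later recall is a poor substitute.
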